**Figure 1 pcn570236-fig-0001:**
[figure not shown]
CONSORT flow diagram showing allocation in the three groups. ICBT, internet‐based cognitive behavioral therapy.

### Randomization

Eligible participants will be randomly assigned to each group at a ratio of 1:1:1, with assignments made using a block randomization method with R' “randomizr” package,^32^ ensuring a balance in baseline Japanese version of the Liebowitz Social Anxiety Scale (LSAS‐j) total scores of <50 or ≥50, sex (male or female), and facilities as adjustment factors. Allocation by using the randomizer will be conducted by the second author ([name]). The randomization sequence will be concealed from researchers at each university, and the statistician will remain blinded to participants' group assignments.

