### Outcome

All outcome measures will be structured as web‐based questionnaires and sent to the participants' email addresses at baseline, post‐intervention (5 weeks follow‐up), 3 months follow‐up, and 6 months follow‐up. To promote participant retention and follow‐up completion, monthly email reminders will be sent from the start of the intervention until the end of the follow‐up period. Any deviations from the trial intervention will be recorded during follow‐up assessments.

The primary outcome will be the GARS used to measure the severity of clinical symptoms and rate anxiety/fear and avoidance of gaze. The GARS comprises 17 items regarding social situations involving focused gaze.^3^ For each item, participants will rate the degree of anxiety/fear and the frequency of avoidance on a scale from 0 (“no anxiety” or “no avoidance”) to 3 (“a lot of anxiety” or “avoid a lot”). The total GARS score ranges from 0 to 102, with higher scores indicating a greater severity of gaze anxiety. The validity and reliability of the GARS have been demonstrated in the original English and German versions.^3^, ^17^, ^18^ The Japanese version of the Gaze Anxiety Rating Scale (GARS‐j) was developed through translation into Japanese by the first author ([name]) and back‐translation by the second author ([name]), with the resulting text being reviewed by the original scale developers (please refer to the GARS‐j in the Supporting Information).^19^ Furthermore, the validity of the GARS‐j will be examined using baseline responses from this trial. Table 3 shows secondary outcomes.

**Table 3 pcn570236-tbl-0003:** Secondary outcomes.

Outcome	Description
LSAS‐j	The LSAS‐j includes 24 social situations related to “fear or anxiety” and “avoidance,” which participants rank on a 4‐point scale (0 = never, 4 = severe), has a total score range of 0–144.^20^ The Japanese version of the LSAS has demonstrated reliability and validity and is widely used in Japanese clinical and research settings.^21^ Therapeutic response will be defined as a ≥28% decrease in the LSAS total score.^22^ Remission will be defined as an LSAS total score of <35,^23^ consistent with a previous RCT.^10^ Conversely, worsening will be defined as a ≥28% increase in LSAS total score to assess the risk of exacerbating social anxiety.

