### Sample size

The sample size for this study was set at 249 (Figure 1), considering the following G*Power estimated values and a 20% attrition rate (version 3.1.9.7; The G*Power Team).^30^, ^31^ We set the parameters for the *F* tests—anova: fixed effects, omnibus, one‐way, with an effect size *F* = 0.25 (medium), an *α* error probability of 0.05, and a power (1 − *β* error probability) of 0.9 for three groups. These inputs yielded a noncentrality parameter of 12.94, a critical *F* of 3.04, an original total sample size of 207, and an actual power of 0.902.

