### Statistical analysis plan

Statistical analyses will be performed by the second author ([name]) using IBM spss Statistics (IBM Corp., Armonk, NY, USA) and will adhere to the intention‐to‐treat principle. The analyst was not involved in creating the two intervention programs. The analyst will be concealed to group allocation when accessing the data. This means she will not know which specific intervention a group received or if each participant was in the control condition.

Descriptive statistics will be used to summarize demographic data (including participants' age and sex) and the severity of clinical symptoms on each scale. Group differences will be compared to determine statistical significance. As a primary analysis, mixed‐effects models will examine significant differences in the mean change in total scores on each symptom rating scale between the groups from baseline to Week 5 (1 month), Week 13 (3 months), and Week 26 (6 months) post‐intervention. If an overall significant difference is found, multiple comparisons will be conducted. For multiple comparisons, we will implement Dunnett's test to control for inflated Type I error rates.^33^ Effect sizes will be calculated between and within the groups. The significance level for hypothesis testing will be set at a two‐tailed *α* of 0.05, and 95% two‐sided confidence intervals will be calculated.

For the binary variables of treatment response, remission, and worsening, the odds and risk ratios between the groups will be analyzed using Fisher's exact test. To further evaluate the risk of worsening social anxiety, as measured by the LSAS, we will calculate the risk ratio, relative risk reduction, absolute risk reduction, and number needed to treat.

We plan to conduct a sensitivity analysis excluding participants with insufficient engagement in the self‐help intervention and those who provided implausible response patterns—specifically, patterns like straight‐lining, contradictory responses, or inconsistent responses between the GARS‐j and the LSAS‐j. Participants will be defined as having sufficient engagement if those in the self‐help book group have completed at least two chapters, and those in the ICBT group have reached the “Behavioral Experiments” treatment module. The sensitivity analysis, similar to the primary analysis, will be performed after imputing missing values using R's “mice” package.^34^

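### The primary comparison is stated as change from baseline, with no baseline GARS or balancing-factor term named; adjusting for them would gain precision at no cost

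*Protocol article*

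**What the plan says.** Three sections of the protocol article bear on this.

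- **Randomization.** Participants are "randomly assigned to each group at a ratio of 1:1:1", with baseline LSAS-j total "scores of <50 or ≥50, sex (male or female), and facilities as adjustment factors". The words on adjustment stand in the sentence about balancing the allocation. They do not describe model terms.
- **Statistical analysis plan.** The primary analysis uses mixed-effects models to examine "significant differences in the mean change in total scores on each symptom rating scale between the groups from baseline to Week 5", and likewise to Weeks 13 and 26. An omnibus result comes first and Dunnett comparisons follow. No covariate is listed: not baseline GARS, LSAS-j stratum, sex or facility. Nothing says that they will be left out either.
- **Sample size.** The calculation is a one-way omnibus ANOVA without covariates, with f = 0.25, an alpha "error probability of 0.05" and a power (1 − beta "error probability) of 0.9 for three groups". It does not say whether f is scaled to the SD of the follow-up score or the SD of change.

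The primary outcome is the GARS total: "The total GARS score ranges from 0 to 102". Entry requires only a score of 10 or more (Participants), so baseline severity may vary widely.

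**The concern.** The section positively chooses change from baseline as the quantity to compare. A raw change score subtracts the whole baseline value. When the baseline-to-follow-up slope is below one this over-corrects: an arm that happens to start higher will tend to fall further, and that chance difference stays in the estimate as noise. Conditioning on baseline removes it. Baseline GARS is not itself a balancing factor; allocation uses a dichotomised score on a different scale, the LSAS-j.

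The second part concerns the restricted allocation. When arms have been forced to balance on factors that predict outcome, an analysis without those factors leaves their variation in the residual. Standard errors are then larger than the design warrants and the test is conservative.

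Precision is what is at stake: wider intervals and lower power than the same participants and the same questionnaires could give.

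**Working it through.** **1. The plan's own figure.** Inputs from Sample size: f = 0.25, three groups, alpha 0.05, N = 207.
- Noncentrality: lambda = N f² = 207 × 0.0625 = 12.94.
- Critical F on 2 and 204 df = 3.04.
- Power = 0.902. N = 204 gives 0.898, so 207 is the smallest multiple of three that reaches 0.90.

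All the stated values reproduce.

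**2. Change score against baseline adjustment.** Take equal variance at baseline and follow-up (scaled to 1) and correlation rho.
- Variance of change: 2(1 − rho).
- Residual variance given baseline: 1 − rho².
- Ratio: (1 − rho)(1 + rho) / [2(1 − rho)] = (1 + rho)/2.

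With unequal SDs s0 (baseline) and s1 (follow-up), the difference is (s0² + s1² − 2 rho s0 s1) − s1²(1 − rho²) = (s0 − rho s1)². This is never negative, so apart from a degree of freedom adjustment does not lose.

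**3. Size if f = 0.25 is on the change-score SD.** At N = 207, lambda becomes 12.94 / ratio, with one df spent on the covariate. Unadjusted power is 0.902 throughout. The values of rho are assumed.

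| rho | variance ratio | saving | adjusted power | N for 90% power, adjusted |
|---|---|---|---|---|
| 0.3 | 0.65 | 35% | 0.984 | 135 |
| 0.5 | 0.75 | 25% | 0.967 | 156 |
| 0.7 | 0.85 | 15% | 0.944 | 177 |
| 0.8 | 0.90 | 10% | 0.931 | 186 |

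Interval width scales with the square root of the ratio: 0.81, 0.87, 0.92 and 0.95.

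**4. Size if f = 0.25 is on the follow-up-score SD.** Power at N = 207, raw change against adjusted: 0.776 against 0.928 (rho 0.3), 0.902 against 0.967 (rho 0.5), 0.990 against 0.996 (rho 0.7).

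**5. Does calling the model mixed-effects already give the gain?** A generalised least squares check used four visits, compound symmetry, complete data and 69 per arm. It compared two models that put baseline among the responses. The table shows the variance of an arm contrast in change.

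| rho | free arm means at baseline | common baseline mean | ratio |
|---|---|---|---|
| 0.3 | 0.0406 | 0.0264 | 0.65 |
| 0.5 | 0.0290 | 0.0217 | 0.75 |
| 0.7 | 0.0174 | 0.0148 | 0.85 |

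The free-means model has exactly the raw-change variance, for example 4(1 − 0.5)/69 = 0.0290. The gain comes only from a baseline covariate or a common baseline mean.

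**6. The balancing factors alone.** As main effects they take 1 (LSAS-j) + 1 (sex) + 11 (12 facilities) = 13 df. If they explain a share R² of residual variance (assumed), power at N = 207 uses lambda = 12.94/(1 − R²). The true size of the unadjusted test is about 2[1 − Φ(1.96/√(1 − R²))].

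| R² | adjusted power | true alpha if omitted |
|---|---|---|
| 0 | 0.902 | 0.050 |
| 2% | 0.908 | 0.048 |
| 5% | 0.917 | 0.044 |
| 10% | 0.931 | 0.039 |

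A full cross would have 2 × 2 × 12 = 48 cells, and 249/48 = 5.2 people per cell over all three arms. That is too thin to model. Main effects are feasible.

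**The case against.** The strongest reply is that this is a condensed article. A mixed model of change can carry baseline, stratum and site terms, and a covariate list is commonly left to the full plan. This stands as far as it goes: a reader might infer that the trial has decided to ignore these variables, and the document does not support that. It is silent on them. What remains is that the article does commit to change from baseline as the compared quantity, and step 5 shows that the mixed-model label alone does not recover the precision.

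A reader might also infer that planned power is being thrown away. It is not. The sample size assumed no covariates, so if f is on the change scale an unadjusted analysis of 207 people keeps its 0.902. The same holds on the follow-up-score scale when rho is 0.5 or more. Adjustment is then a bonus.

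A third tempting reading is that omitting the balancing factors biases the result. It does not; the cost is efficiency and a conservative test. Nor should the attrition allowance be used as support. About 199 people (249 × 0.8) would remain, with power 0.890, but how 249 was reached is a separate matter.

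Finally, the size of the gain cannot be fixed from the document, and at high rho it can be negligible (0.990 against 0.996).

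**Conclusion.** The point holds as a free improvement. The primary comparison as written is valid, but it is less precise than a baseline-adjusted one. The variance saving is about 10% to 35% for an assumed rho of 0.8 to 0.3, with equal variances over time. What this means for power depends also on the SD scale of f, which is not given. Baseline GARS is likely to supply most of the gain; the balancing factors add a smaller amount that depends on how strongly they predict outcome. The document does not show that these terms will be excluded, that the estimate is biased or that planned power is lost.

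**What to change.** State the primary model in full:

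- GARS total at Weeks 5, 13 and 26 as the repeated outcome;
- fixed effects of arm, visit and arm × visit;
- baseline GARS and baseline GARS × visit as covariates or, as an equivalent route to the same gain, baseline among the responses with one mean common to the three arms;
- LSAS-j stratum (<50 or ≥50) and sex as fixed main effects;
- facility as a random intercept or main effect, without the full cross of strata.

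Take the arm contrasts from this model. Participants are also recruited through the project website, so say which facility level they carry in the model.

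Fix the specification before outcome data are seen by arm. The cost is wording only: baseline GARS, LSAS-j, sex and facility are all available before allocation, no further data are needed, and the sample size need not change.

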### Blinding

This trial will not be blinded.

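### One role both runs the allocation and analyses the data, so the stated blinding of the analyst is not secured as written

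*Protocol article*

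**What the plan says.** The relevant statements are in two sections of the protocol article.

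- Randomization, on who allocates: "Allocation by using the randomizer will be conducted by the second author".
- Randomization, immediately afterwards: "The randomization sequence will be concealed from researchers at each university", and "the statistician will remain blinded to" participants' group assignments.
- Statistical analysis plan, on who analyses: "Statistical analyses will be performed by the second author".
- Statistical analysis plan, on what the analyst knows: "The analyst will be concealed to group allocation when accessing the data", explained as "This means she will not know which specific intervention a group received or if each participant was in the control condition".
- Statistical analysis plan, on independence: "The analyst was not involved in creating the two intervention programs".

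The Statistical analysis plan section also sets out an intention-to-treat primary analysis by mixed-effects models, with Dunnett comparisons if the overall test is significant. A sensitivity analysis then removes participants with too little engagement and those whose answers look implausible.

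**The concern.** The article assigns allocation and analysis to one role and then says that this role does not know the allocation. If the statements stay as they are, the results paper is likely to repeat a claim of analyst blinding that the described procedure does not support.

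Outcomes are self-rated and participants know their arm, so the claim adds to the credibility of the result. It matters most where the analysis leaves room for judgement. The sensitivity analysis does so, because it removes implausible responders by example rather than by rule, and the Discussion relies on the sensitivity analyses to show that the primary result is robust. Exclusions made with knowledge of the arm would weaken that argument.

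**Working it through.** No arithmetic applies. The check sets the statements side by side.

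1. **Same role.** The allocator in "Allocation by using the randomizer will be conducted by the second author" and the analyst in "Statistical analyses will be performed by the second author" are both the second author. The statistician of the Randomization section is not otherwise identified, and the only person named as doing the statistics is again the second author.

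2. **What the allocator has.** The method is block randomization in R, balanced on baseline LSAS-j total (below 50, or 50 and above), sex and facility. Running it takes each participant's stratum as input and returns one assignment per participant. Unless the output carries only coded labels and someone else holds the key, the person who runs it knows who is in which arm.

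3. **What the blinding statements claim.** "This means she will not know which specific intervention a group received or if each participant was in the control condition" covers two levels: the identity of each group and the control status of each participant. A participant-level list with named arms defeats both.

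4. **Whether a stated safeguard closes the gap.** Concealment of the sequence is stated only for site staff, and cannot cover the person who generates it. The independence statement, "The analyst was not involved in creating the two intervention programs", concerns development of the programs, not allocation. No separate code-holder, relabelling of arms or division of the two tasks is described.

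5. **Where knowledge of the arm could act.**
   - *Outcome measurement:* not through the analyst. Participants complete web questionnaires.
   - *Primary analysis set:* intention to treat, with no exclusions stated.
   - *Response-pattern exclusions (sensitivity analysis):* described by examples (uniform answering, self-contradiction, disagreement between GARS-j and LSAS-j) with no threshold.
   - *Engagement exclusions (sensitivity analysis):* at least two chapters for the book arm; reaching the Behavioral Experiments module, the fifth of ten in Table 2, for the ICBT arm; no criterion for controls. According to the Adherence section, chapters are self-reported and modules are logged by the system. Anyone who applies this rule to the raw adherence data therefore sees the arms.

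Moving the allocation to someone else is thus necessary but not sufficient. The raw adherence fields must also be kept from the analyst.

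**The case against.** The strongest reply is that the wording suggests coded arms. The concealment is claimed for the time of accessing the data, and it is explained as not knowing which intervention a group received. An allocator who assigns coded groups, with the study secretariat holding the key, would fit that, and custody of codes is a detail that an article may leave to the full protocol. This stands in part: one cannot say that blinding is impossible or absent, only that it is not secured by what is written. It does not remove the point, because the article states both halves of the conflict itself.

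It is also fair that the article does not say who decides the exclusions. That the analyst does so is an inference from her being the person who performs the analyses.

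A reader might draw three stronger conclusions that the document does not support.

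- That "This trial will not be blinded" in the Blinding section flatly contradicts analyst blinding. The sentence can refer to participants and site staff, as is usual in an open trial with a blinded analyst.
- That Dunnett's test by itself unblinds the analyst. It is run only after a significant overall result, so the control code is needed only at that last step, and everything before it can be done on coded arms.
- That discretionary exclusions threaten the primary result. They are confined to the sensitivity analysis. A numerical shift in an arm mean would need a removal rate and an outcome deficit among those removed, and the document gives neither.

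**Conclusion.** The role assignments in the Randomization and Statistical analysis plan sections contradict the blinding that the same sections claim. As written, analyst blinding is not secured and should not be reported as a feature of the trial.

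The consequence is limited to two blinding statements that need correcting, to analyst choices in general, and to one sensitivity analysis with open-ended response-pattern exclusions and an arm-specific engagement rule. No effect on the composition of the intention-to-treat primary set is shown, and no numerical size can be given from the document.

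The conclusion assumes that the second author is the same person in both sections, as the wording says, and that no undescribed coding procedure separates the two tasks. If such a procedure exists, stating it would resolve much of the point. Nothing here implies improper conduct.

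**What to change.** If allocation has not yet been run:

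- Have an existing team member other than the analyst run the allocation and hold the list.
- Give the analyst the arms coded A, B and C, with a prepared 0/1 engagement flag in place of the raw chapter and module data. Controls have no engagement criterion, so a flag with no failures in one arm could point to the control group. It is best released after the response-pattern exclusions are settled.
- Fix rules with thresholds for implausible responses. Lock those exclusions and the analysis syntax before the control code is released for the Dunnett comparisons.

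If the analyst has already run the allocation, which is possible because the Results section schedules registration for April 1 to May 31, 2025:

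- Withdraw the blinding statements in the Randomization and Statistical analysis plan sections.
- Have a colleague without access to the list make the response-pattern exclusions by rules fixed in advance.

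The cost is a task reassigned within the existing team and a few sentences of wording. Sample size, data collection and staffing do not change.

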### Blinding

This trial will not be blinded.

### Adverse events

We will instruct all participants at each university to immediately report any adverse events that occur during this trial period. If additional support is needed, participants will be referred to campus counseling services or encouraged to visit local clinics affiliated with their universities. Even if no adverse events are reported, participants scoring 10 or above on the Patient Health Questionnaire‐9 (PHQ‐9) total score during the follow‐up period will assess their mental health problem by using the MINI.^13^, ^26^ Based on the results of this assessment, participants may be recommended to see a medical doctor.

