#### Self‐help in ICBT group

Participants allocated to this intervention group will be instructed to engage using their own devices in an ICBT program designed to ameliorate social anxiety in adolescents and young adults. The completion of one module per week will be recommended, and automated email reminders encouraging program engagement will be sent to participants every Monday morning. The ICBT program was developed by the first author ([name]) on the e‐learning platform learningBOX (learningBOX Inc., Tatsuno, Japan). The ICBT program is based on the model proposed by Clark and Wells.^16^ The program comprises 10 training sessions focusing on CBT components that are efficacious for SAD. Each module is expected to take about 15 min to complete, and the entire content can be finished in about 150 min. Table 2 outlines the treatment modules of the ICBT program.

**Table 2 pcn570236-tbl-0002:** Treatment module of the internet‐based cognitive behavioral therapy (ICBT) program.

Week	Module
1	Psychoeducation and case‐formulation using the cognitive behavioral model
2	Examining safety behaviors and self‐focused attention
3	Video feedback to correct negative self‐image
4	Attention shift training
5	Behavioral experiments
6	Opinion survey
7	Ceasing rumination and pre‐ and post‐event processing
8	Processing social trauma in image description
9	Schema work
10	Relapse prevention

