### Adherence

We will assess adherence to the two interventions using two methods. In the book group, participants will be asked to report the chapters of the self‐help book read and cognitive‐behavioral techniques practiced in daily life at the initial outcome assessment. For the web‐based CBT intervention, the e‐learning system will record completed treatment modules automatically, and participants will also report cognitive‐behavioral techniques practiced in daily life at the initial outcome assessment. All participants, including the control group, will be asked to report any unintended treatments or care received during the study period.

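### Adverse events outside the PHQ-9 and LSAS checks are, as described, recorded only if volunteered; one common questionnaire item would make them countable

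*Protocol article*

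**What the plan says.** All places are in the protocol article.

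- **Adverse events.** Everyone is told to "immediately report any adverse events that occur during this trial period". The section then adds a check that needs no report: "Even if no adverse events are reported, participants scoring 10 or above on the Patient Health Questionnaire" are to be assessed with the MINI.
- **Outcome, Table 3.** A second harm measure comes from the common questionnaires: "worsening will be defined as a ≥28% increase in LSAS total score to assess the risk of exacerbating social anxiety".
- **Statistical analysis plan.** The only planned between-group harm analysis is of LSAS worsening, for which "we will calculate the risk ratio, relative risk reduction, absolute risk reduction, and number needed to treat".
- **Outcome.** Web questionnaires go to all arms after 5 weeks, 3 months and 6 months, and "monthly email reminders will be sent from the start of the intervention" to the end of follow-up.
- **Intervention.** The book arm gets an automated announcement each Monday, with five chapter-weeks in Table 1. In the ICBT arm, "automated email reminders encouraging program engagement will be sent to participants every Monday morning", with ten module-weeks in Table 2. No weekly message is described for controls.
- **Adherence.** All participants, controls included, "will be asked to report any unintended treatments or care received during the study period".
- **Blinding.** "This trial will not be blinded".

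**The concern.** The article asks participants directly about outside care and, in the active arms, about chapters read or techniques used. For adverse events it describes only an instruction to come forward. Unprompted reporting usually misses events, and here whether an event is reported may also depend on the arm. Participants know their allocation, only the active arms have a programme to attribute an event to, and only the active arms hear from the trial every week.

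Both programmes are used without a therapist and include video feedback, behavioural experiments and processing of social trauma. The Ethics section acknowledges that the material concerns thoughts, habits and situations that participants may find distressing. If few or no events are reported, the results paper may be read as showing that the programmes are safe. If the counts differ by arm, they may be read as showing harm or protection. The collection method described supports neither reading. The primary analysis of the GARS is not affected.

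**Working it through.** The article gives no adverse-event rate or reporting rate, so there is no figure of its own to reproduce. Every event and reporting rate below is an assumption.

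**1. What each safety source can capture**
- PHQ-9 of 10 or above: depressive symptoms at scheduled time points, followed by a MINI. Same in all arms.
- LSAS rise of 28% or more: social anxiety at scheduled time points. Same in all arms.
- GARS, SPIN and GAD-7: collected on the same schedule, but no worsening threshold is stated for them.
- Question on outside care: may reveal events that led to care, but does not ask about events.
- Adverse events as such (for example, acute distress after an exercise, and when it occurred): volunteered reports only.

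Timing matters too. In Table 2, social-trauma processing is Week 8 and schema work is Week 9. Both fall between the questionnaires at Week 5 and Week 13, so a transient reaction that resolves by Week 13 is seen only if volunteered.

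**2. Scheduled contacts per arm** (about 6 monthly reminders assumed, plus 3 post-baseline questionnaires)
- Book: 5 + 6 + 3 = 14
- ICBT: 10 + 6 + 3 = 19
- Control: 0 + 6 + 3 = 9

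Contact is unequal, but the excess consists of automated engagement messages in the first 5 to 10 weeks.

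**3. Under-ascertainment, with no difference between arms**
- Per arm: 249 / 3 = 83.
- True risk 10%, half of events reported everywhere: 83 × 0.10 = 8.3 events, of which 8.3 × 0.5 = 4.2 are seen. The risk ratio stays at 1.0.
- No reports in an arm: the one-sided 95% upper limit p for the reported risk solves (1 − p)^83 = 0.05, so p = 1 − 0.05^(1/83) = 3.5%.
- Dividing by the reporting probability gives the limit for the true risk: 3.5% / 0.6 = 5.9%; 3.5% / 0.3 = 11.8%.

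**4. What would follow if reporting did differ by arm** (equal true risk of 10%)
- 60% v 40%: 83 × 0.10 × 0.60 = 5.0 and 83 × 0.10 × 0.40 = 3.3 reports; risk ratio 0.60 / 0.40 = 1.5.
- 60% v 30%: 5.0 and 2.5 reports; risk ratio 2.0. Fisher's exact test at 5% would be falsely significant in 6.6% of trials (1.3% at a true risk of 5%, about 20% at a true risk of 20%).

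The true risk cancels, so the spurious risk ratio is simply the assumed reporting ratio. It illustrates a mechanism and is not an estimate.

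**5. A milder version of step 4.** Suppose reporting is 60% only while weekly messages run and 30% otherwise, with events spread evenly over 26 weeks.
- ICBT: (10 × 0.6 + 16 × 0.3) / 26 = 0.415; risk ratio 0.415 / 0.30 = 1.38.
- Book: (5 × 0.6 + 21 × 0.3) / 26 = 0.358; risk ratio 0.358 / 0.30 = 1.19.

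Events clustered early would raise these ratios.

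**The case against.** The case on the other side is substantial.

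- A reader might infer that safety rests only on spontaneous reports. It does not. The PHQ-9/MINI check works without any report, LSAS worsening is measured alike in all arms, and other symptom scales and the outside-care question add information. This stands, and it limits the point to adverse events as such.
- A reader might infer that the trial's safety comparison is biased. The article plans no between-arm comparison of reported adverse events. The comparison it does plan, LSAS worsening, depends on neither volunteered reports nor weekly messages, although it is self-rated in an open trial. This stands.
- A reader might infer that unequal contact distorts reporting, perhaps twofold. The reporting instruction is the same for everyone, and the weekly messages are not described as asking about harm. A difference between arms is neither shown nor excluded, and its direction is uncertain. The ratio of 2.0 restates its own input and applies it to the whole trial. This also stands.
- The article is a condensed account, and adverse-event items may sit in the full protocol. This stands only in part. The article does not merely omit the method: it states one, participant-initiated reporting, while describing direct questions on other matters.
- A solicited question is still self-report by people who know their arm. True, so the remedy is partial. It does equalise the prompting, and it does not rely on participants to come forward unasked.

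**Conclusion.** The point holds in a limited form. As described, adverse events other than a PHQ-9 of 10 or above and LSAS worsening are captured as such only when participants volunteer them. Under-ascertainment is therefore probable in every arm, and this conclusion needs no difference between arms. If 60% to 30% of events are reported, an arm of 83 with no reports would still be compatible with a true risk of up to about 5.9% to 11.8%, against 3.5% if every event were reported. These figures rest on the assumed reporting rates and on all 83 participants being in a position to report.

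Any between-arm reading of reported counts would be unreliable, because the trial is open and contact differs by arm. The documents do not show that reporting will differ, and no such comparison is planned. The planned analyses are not invalidated. The weakness lies in whatever the trial later says about adverse events in general.

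**What to change.** Add one identical adverse-event item, yes/no plus free text, to the Week 5, 3-month and 6-month web questionnaires in all three arms. It should ask about the time since the previous questionnaire, so that the later ICBT modules are covered. Summarise these solicited events by arm, list spontaneous reports separately, and state that the spontaneous counts are not compared between arms. If the full protocol already contains such an item, a sentence saying so is enough. If some questionnaires have already gone out, add the item to all that remain, in every arm alike.

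The cost is a minor amendment and one extra item in questionnaires already being sent, with no extra visits or staff. Respondents carry slightly more burden and there will be more events to list. Some attribution bias remains, since participants know their arm. The change touches neither the immediate-reporting instruction nor the PHQ-9/MINI procedure.
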